### Study design

A cRCT comparing the proactive diabetes review model (PDRM) to usual care (reactive review) and parallel process evaluation (Fig. 1). The schedule of enrolment, interventions and assessments are detailed in Fig. 2. The SPIRIT checklist [5] which details the recommended content for a protocol has been included as Additional Paper 1.

**Fig. 1 Fig1:**
[figure not shown]
A cRCT comparing the proactive diabetes review model (PDRM) to usual care (reactive review) and parallel process evaluation

**Fig. 2 Fig2:**
[figure not shown]
Schedule of enrolment, interventions and assessments

A cRCT randomly allocates an intervention to a cluster or group of individuals within a cluster [24]. Cluster randomised controlled trials are appropriate when it is not possible to randomise at an individual level. In this study, individual randomisation was not appropriate due to the risk of contamination between and across individuals either directly with each other or through the staff providing their care [1, 10].

### Feasibility trial

#### The trial

Eight wards will be recruited with four randomised to receive the PDRM intervention and four usual care. As this is a feasibility trial, a formal power calculation is not indicated and has not been undertaken. The sample size of eight wards is a pragmatic choice to allow sufficient recruitment across inpatient specialities, whilst not recruiting wards unnecessarily. All wards will undergo an 8-week run-in period to allow a period of ‘settling in’. This aims to allow all the PDRM DISNs time to become familiar with the process and trial-related activities prior to data collection. A 24-week intervention/data collection period will then begin.

#### Trial population and eligibility

There will be eligibility and recruitment at two levels: ward (clusters) and patients (within clusters).

##### Wards

Eight general adult medical and surgical wards will be recruited. Specialist diabetes wards, day-case units, maternity and paediatric wards will be excluded.

Recruitment of wards will happen at the divisional and ward levels. A division is made up of closely allied specialities and services that operate within a common governance structure to deliver seamless patient pathways. A specific information sheet is developed for divisional leads and ward managers. Divisional lead approval will be sought. Following approval, ward managers and clinical leads of wards identified as eligible for inclusion will be approached for recruitment.

##### Patients

Adult inpatients with a diagnosis of diabetes documented on their problem list and admitted to one of the included wards will be eligible. They will be identified via a daily report run by the diabetes specialist team administrator. Inpatients already under the care of the specialist diabetes team in the hospital will be excluded. Eligible patients will be approached during their hospital stay for recruitment and to obtain informed consent for the use of their data and provided with an information sheet.

#### Randomisation

Randomisation will be stratified by ward type (medical or surgical). Wards will be randomly allocated to receive either usual care or the PDRM intervention. The Ralloc procedure in Stata® will be used. Block randomisation will limit imbalance in trial arms. Randomisation will take place following ward recruitment and study team training.

#### Usual care

Wards randomised to receive usual care will receive a reactive review by a DISN on receipt of a referral by a member of the primary team (patients admitting speciality doctor and ward nurses) or if highlighted through the daily high-risk report. Both are current usual practices in the participating site. The structure of the review undertaken, recommendations made and frequency of follow-up will be as per current local practice.

##### Patient identification

A daily electronic report will identify all admitted patients with diabetes in an included ward. Once identified, for patients in an intervention ward, the DISN will complete an initial remote assessment to establish whether a PDRM review is appropriate. Examples of potential exclusions would be if a diabetes medical review is required (where there is diagnostic uncertainty or complex medical needs) or if a PDRM is not required (where a patient is in the last hours of life or due for imminent discharge and no diabetes-related concerns).

#### Approach and consent

There are known practical challenges to receiving informed consent at an individual patient level in a cluster randomised design [3] and [18]). This has been explored through a review of other cluster randomised designs [24], [25], [15] and [18]) and seeking patient, public and expert opinion through patient and public involvement activities. The consent process as described has been designed to meet both the legal and ethical requirements for research whilst also considering potential risks associated with the methodology used.

Individual patient informed consent will be sought for the collection of patient-identifiable data. Permission for the delivery of the PDRM intervention in the clinical area will be obtained from the ward manager and clinical lead prior to ward-level randomisation.

Receipt of the PDRM intervention does not equate to participant inclusion in the study, and declining the PDRM intervention does not exclude patients from being eligible for the trial.

By separating these processes, patients will be able to receive (or refuse) a diabetes review in line with usual clinical care, even if they do not consent to their data being included in the study. Equally, patients can opt to have their data included even if they did not wish to receive the PDRM intervention.

#### Outcomes

Given the feasibility design of this study, outcomes have been split into two categories: (1) feasibility and process and (2) trial.

#### Feasibility and process outcomes

The following are the feasibility and process outcomes:Proportion of wards recruited against the target Proportion of approached and eligible patients that are recruitedProportion of eligible patients on the ward seen by a diabetes specialist during their admissionTime from admission to an included intervention ward to receiving a review by a diabetes specialist

#### Trial outcomes

The following are the trial outcomes:Number of days, per patient admission, where glucose testing completedIncidence of hypoglycaemia (rate of biochemical hypoglycaemic episodes defined as blood glucose < 4.0 mmol/L during hospital stay)Incidence of hyperglycaemia > 15.0 mmol/LIncidence of positive ketones (blood ketone ≥ 1.5 mmol/L)Incidence of hospital-acquired foot ulcerationLength of hospital stay (total number of inpatient days)

The feasibility of a future definitive trial will be determined by the following:Evidence that recruitment at both the cluster and individual levels can be achievedEvidence that the intervention can be delivered. The proportion of patients who received the proactive reviewEvidence of availability of trial outcome data

We will analyse our feasibility data for recruitment and intervention delivery against the progression criteria as set out in Table 2. Where the criteria set out in the green column are met, the study will be considered feasible. If only the criterion in the amber column is met, feasibility will be dependent on whether a definitive trial could address this methodologically, drawing on the process evaluation data. If the amber criteria are not met, the study will not be considered feasible. For progression to a definitive trial, the findings must demonstrate that all five green or amber criteria have been met, with strategies to address where we have not met green criteria.

**Table 2 Tab2:** Progression criteria

	Green	Amber	Red
Cluster recruitment to target (8 wards)	90–100%	70–89%	< 70%
Participant recruitment: proportion of approached and eligible patients consenting to participate	90–100%	70–89%	< 70%
Intervention delivery: proportion of patients that received the intervention (intervention arm participants only)	90–100%	70–89%	< 70%
Median time from identification to receiving a review by a diabetes specialist (intervention arm participants only)	Within one working day	One to three working days	Four or more working days
Trial outcome data available	90–100%	70–89%	< 70%

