**Method:**

We will conduct a cluster randomised feasibility study with process evaluation. The proactive diabetes review model (PDRM) is a complex intervention that focuses on the prevention of potentially modifiable diabetes-related harms. All eligible patients will receive a comprehensive, structured diabetes review that aims to identify and prevent potentially modifiable diabetes-related harms through utilising a standardised review structure. Reviews are undertaken by a diabetes inpatient specialist nurse within one working day of admission. This differs from usual care where patients are often only seen after diabetes-related harms have taken place. The trial duration will be approximately 32 weeks, with intervention delivery throughout. There will be an initial 8-week run-in phase, followed by a 24-week data collection phase. Eight wards will be equally randomised to either PDRM or usual care. Adult patients with a known diagnosis of diabetes admitted to an included ward will be eligible. Data collection will be limited to that typically collected as part of usual care. Data collected will include descriptive data at both the ward and patient level and glucose measures, such as frequency and results of capillary glucose testing, ketonaemia and hypoglycaemic events. The analysis aims to determine the fidelity and acceptability of the intervention and the feasibility of a future definitive trial. Whilst this study is primarily about trial feasibility, the findings of the process evaluation may lead to changes to both trial processes and modifications to the intervention. A qualitative process evaluation will be conducted in parallel to the trial. A minimum of 22 patients, nurses, doctors, and managers will be recruited with methods including direct non-participant observation and semi-structured interviews. The feasibility of a future definitive trial will be assessed by evaluating recruitment and randomisation processes, staffing resources and quality of available data.

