## The intervention—proactive diabetes review model (PDRM)

The proactive diabetes review model (PDRM) is a complex intervention that combines all the components of the usual care provided by a DISN at the first review, and applies the principles recommended by the national quality board by making changes to the timing, focus and ambition of the review. PDRM will be delivered by DISNs for patients with diabetes admitted to the hospital. The PDRM consists of a patient-centred diabetes assessment undertaken within one working day of admission to an included intervention ward and aims to identify modifiable risks and prevent diabetes-related harm (see Table 1). The intervention will consist of a single visit for individual patients; all care after this will fall in line with usual care. Recommendations will be based on best clinical practice, at the discretion of the professional undertaking the review.

**Table 1 Tab1:** PDRM intervention components

Category	Detail	Outcome data source
An initial bedside assessment of the patient	Current and historical medications Feet and injection sites as appropriate Usual diabetes care provider Diabetes education history Patient-reported history of home glucose level	Reviewing the medical notes and trial paper case report forms
A review of routinely collected investigations	Glucose monitoring Ketone monitoring where applicable HbA1c Annual review processes, TSH, urea, creatinine, ACR	Reviewing the medical notes and electronic data exports
Recommendations resulting from the shared decision-making process	Links to relevant policies and guidance where appropriate Documented in the patients’ medical records	Reviewing the medical notes and trial paper case report forms
Provision of any appropriate patient information	Leaflets App recommendations Other patient literature Signposting to any relevant patient-specific resources	Reviewing the medical notes and trial paper case report forms
Handover of recommendations to the patient and patient’s primary team	Admitting speciality doctor Ward nurses	Reviewing the medical notes and trial paper case report forms
Triage	No further follow-up Further follow-up by the diabetes specialist team—ongoing reviews will be managed in line with usual care	Reviewing the medical notes and trial paper case report forms

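### The timeliness progression criterion counts from identification, but the intervention and its feasibility outcome count from ward admission, so a service that misses its own timing definition can score green

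*Protocol article*

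**What the plan says.** The protocol article gives the timing of the review in several places, and they do not share a starting point.

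- **Abstract, Method:** "Reviews are undertaken by a diabetes inpatient specialist nurse within one working day of admission".
- **The intervention section:** the assessment is "undertaken within one working day of admission to an included intervention ward".
- **Feasibility and process outcomes:** the timing outcome runs from admission to an included intervention ward up to the specialist review.
- **Trial outcomes, Table 2:** the progression criterion is "Median time from identification to receiving a review by a diabetes specialist (intervention arm participants only"). Its bands are "Within one working day" (green), "One to three working days" (amber) and "Four or more working days" (red).

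Identification is described as its own step. Under Patient identification, "A daily electronic report will identify all admitted patients with diabetes in an included ward". Under Trial population and eligibility, Patients, "They will be identified via a daily report run by the diabetes specialist team administrator", and eligibility depends on diabetes being recorded on the problem list. The article nowhere says that identification and admission are to be treated as the same moment.

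The text above Table 2 requires all five criteria to be green or amber before a definitive trial, with strategies for any criterion that is not green.

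**The concern.** Promptness is one of the features that distinguish PDRM from usual care, and the article ties it to ward admission. The timing row is the only progression criterion that states a time limit, yet its clock starts later. It therefore tests how quickly nurses respond once a patient appears on the list. It does not test whether the whole pathway, including getting the patient onto the list, delivers the review as defined. Whether patients can be identified in time is itself a feasibility question, and this row cannot see it.

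At stake is whether a timeliness problem is recognised in the progression decision. A green score means that no remedy has to be designed for the definitive trial. An amber score means that one does.

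**Working it through.** The plan gives no figure to reproduce here. The check compares the definitions and then scores the same review times on both clocks.

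**1. Inputs**

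- Target: one working day from admission to the included ward (intervention section).
- Scored quantity: median time from identification to review (Table 2).
- Bands as printed: green at most 1, amber 1 to 3, red 4 or more working days.
- L, the delay from ward admission to identification: **not stated**. Assumed 0 to 1 working day, the range one would expect from a once-daily report. Late entry on the problem list, or a day on which the report is not run, could lengthen it.
- R, the time from identification to review: **not stated**. Set at 0.75 working day for illustration.

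**2. Formula**

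For one patient, time from admission = L + R, while Table 2 counts only R. The two clocks disagree about green whenever R ≤ 1 and L + R > 1.

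**3. Same L and R for every patient**

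| L (assumed) | R | Table 2 score | From admission, same bands |
|---|---|---|---|
| 0 | 0.75 | 0.75, green | 0 + 0.75 = 0.75, green |
| 0.5 | 0.75 | 0.75, green | 0.5 + 0.75 = 1.25, amber |
| 1 | 0.75 | 0.75, green | 1 + 0.75 = 1.75, amber |

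**4. L varying between patients**

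If L is spread evenly over 0 to 1 working day and R is 0.75 for all, the median from admission is 0.5 + 0.75 = 1.25 (amber). The share reviewed within one working day of admission is P(L ≤ 1 − 0.75) = 25%. Table 2 still shows 0.75, green.

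**5. When would the go/no-go result change?**

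Using constant L and R as in step 3, the time from admission must reach 4 working days while Table 2 is green or amber.

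- From green (R ≤ 1): L ≥ 4 − 1 = 3 working days.
- From amber (R ≤ 3): L ≥ 4 − 3 = 1 working day, and that minimum applies only if review already takes three working days after identification.

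Neither fits a working daily report combined with prompt reviews.

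**6. The bands**

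| Median, working days | Bands met as printed |
|---|---|
| 0.5 | green |
| 1 | green and amber |
| 2 | amber |
| 3 | amber |
| 3.5 | none |
| 4 | red |

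A median of 3.5 can occur even when time is counted in whole days, if the two middle values of an even-sized sample are 3 and 4.

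**The case against.** The strongest reply is that little turns on this. Four parts of it deserve an answer.

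- **Amber also permits progression.** This stands. A reader might infer that the wrong clock could send an infeasible trial forward. The documents do not support that: step 5 of the working shows that it needs either a very long identification delay or reviews that are already slow.
- **The delay is not hidden.** The feasibility outcomes already include time from ward admission to review, so the lag would show beside the Table 2 result. This stands as mitigation. It does not change what the decision rule scores.
- **Late reviews might fail the intervention-delivery row**, because the intervention is defined with its time limit. That is possible, but the row does not say whether a late review counts as received.
- **The lag is assumed.** This stands, and with no lag there is no discrepancy. Against a one-day target, however, even half a day matters.

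Three further inferences should be resisted. The overlapping bands do not let a late service score green; the clock alone does that, and the overlap only leaves an on-target median ambiguous. On a natural reading, the green band includes exactly one day. Nothing shows that one working day is the likeliest median, since the target is an upper limit. And nothing says that patients who leave without a review are dropped from the median. Non-receipt has its own row in Table 2, and handling within the median may be set out in a fuller document.

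**Conclusion.** The mismatch is plain from the article and is wrong as written: the progression rule does not measure the timing that defines the intervention. A service late by the protocol's own definition can be scored green.

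The size depends on a delay that the documents do not give. It is nil at zero lag. At an assumed lag of 0.5 to 1 working day with 0.75 working day to review, the score is 0.75 (green) where the time from admission is 1.25 to 1.75 (amber). The usual consequence is green in place of amber, and so the loss of a required mitigation strategy, rather than a wrong decision to proceed. The shared value at one working day and the gap between three and four are secondary wording faults. The point merits correction but is less than a must-fix.

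**What to change.** - Restate the Table 2 timing row as the median time from admission to the included ward to the review, in line with the intervention section and the feasibility outcome.
- Make the bands exclusive and exhaustive: green at most 1, amber more than 1 and under 4, red 4 or more working days.
- Report admission-to-identification and identification-to-review separately as process measures, so that a slow pathway can be traced to listing or to nurse response.

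The cost is one table row. The listed feasibility outcome already needs the admission and review times, and the present criterion already needs the identification time, so no new data are required. The downside is that the timeliness figure may look less favourable.

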#### Data collection

Descriptive and outcome data will be collected throughout the 8-week run-in period and 24-week intervention and follow-up period. To reduce patient burden, a pragmatic approach to data collection will be adopted by restricting all quantitative data to information routinely collected as part of clinical care. Data will be extracted after the participant has consented and the episode of care completed (i.e. after hospital discharge). Data extraction will include a mix of reviewing the medical notes, electronic exports and trial paper case report forms. Ward-level data will be provided by the ward managers through a spreadsheet requested monthly.

Descriptive statistics and outcome measures will be described at baseline (run-in phase) and trial end. Data will be collected for the duration of a participant’s hospital stay. Their inclusion in either the baseline or trial end analysis will depend on the time point of their admission during the trial. Baseline analysis will use the data of participants admitted during the run-in phase (weeks 0–8) and outcome analysis of the data of those participants admitted during weeks 9 to 36.

#### Statistical analysis

Groups at baseline will be described using summary statistics at both ward and patient levels. Changes from baseline will be described within and between the two trial arms from run-in to follow-up periods. The purpose of the analysis is (1) to describe the potential effect via confidence intervals allowing for the clustered design, (2) as a way of trialling an analytic plan for a future definitive trial if the proposed study suggests one is feasible and (3) the extent and distribution of missing data will be reported for consideration as to how to manage this in a definitive trial. Statistical analysis will be completed using the latest version of STATA® with the trial statistician (AC). No interim analysis of trial outcomes between arms is planned.

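### The run-in serves as baseline although the abstract has PDRM delivered throughout the trial, so the planned change-from-baseline contrast attenuates the effect, possibly to zero

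*Protocol article*

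**What the plan says.** All references are to the protocol article.

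- **Abstract, Method:** "The trial duration will be approximately 32 weeks, with intervention delivery throughout". The same paragraph gives the phases: "There will be an initial 8-week run-in phase, followed by a 24-week data collection phase".
- **The trial:** the purpose of the run-in is settling in: "This aims to allow all the PDRM DISNs time to become familiar with the process and trial-related activities prior to data collection". The next sentence is "A 24-week intervention/data collection period will then begin".
- **Randomisation:** "Randomisation will take place following ward recruitment and study team training". Its order relative to the run-in is not given.
- **Data collection:** "Descriptive and outcome data will be collected throughout the 8-week run-in period and 24-week intervention and follow-up period". On the analysis sets: "Baseline analysis will use the data of participants admitted during the run-in phase", given as weeks 0 to 8. Outcome analysis takes admissions in weeks 9 to 36.
- **Statistical analysis:** "Changes from baseline will be described within and between the two trial arms from run-in to follow-up periods". The listed purposes include describing the potential effect with confidence intervals that allow for clustering, and rehearsing the analysis for a definitive trial.

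No data window before the intervention is described for the trial.

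**The concern.** A baseline should precede treatment. On the abstract's wording, patients admitted to PDRM wards in weeks 0 to 8 are already exposed to PDRM, and the run-in's purpose of letting the nurses get used to the process points the same way. Subtracting their outcomes from those of later patients removes whatever part of the effect was already present. The between-arm change would then describe only what was gained after week 8.

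The within-arm change is harder still to interpret. The two periods contain different patients, assigned by admission date, so it also carries case mix, calendar time and the nurses' learning. A baseline description by arm would compare wards already receiving PDRM with wards that are not.

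At stake are two stated purposes of the analysis: the interval for the potential effect, and the analysis template handed on to a definitive trial.

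**Working it through.** The plan states no effect size, power or alpha, so there is no figure of its own to reproduce. The check is algebraic, with illustrations on assumed values.

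**Inputs from the article.** Run-in 8 weeks and follow-up 24 weeks (Abstract; The trial). Baseline is run-in admissions (Data collection). The contrast is run-in to follow-up, within and between arms (Statistical analysis). Expected recruitment is 250 to 500 over 8 wards (Sample size).

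**Assumptions.** E is the full PDRM effect. f is the fraction of E already present on PDRM wards in run-in (not given; range 0 to 1). T is a time trend common to both arms. Usual-care wards have no PDRM effect.

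**Step 1: what each contrast estimates.**
- Change in the PDRM arm: (E + T) - fE = (1-f)E + T.
- Change in the usual-care arm: T.
- Between-arm difference in change: (1-f)E.
- Between-arm difference in follow-up alone: E, whatever f is.

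**Step 2: size on the log scale.** With an assumed true rate ratio of 0.70, the ratio seen is 0.70^(1-f).

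| f | Ratio seen | Share of log effect kept |
|---|---|---|
| 0 | 0.70 | 100% |
| 0.5 | 0.84 | 50% |
| 0.75 | 0.91 | 25% |
| 1 | 1.00 | 0% |

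**Step 3: size on the absolute scale.** With assumed risks of 20% under usual care and 14% under PDRM, E = -6 points. The difference in change is -6.0, -4.5, -3.0, -1.5 and 0 points for f = 0, 0.25, 0.5, 0.75 and 1.

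**Step 4: precision.** If recruitment is proportional to time, the within-ward sampling variance of a change score relative to follow-up alone is (1/24 + 1/8)/(1/24) = 4. This is only the within-ward component, because a change score also removes stable differences between wards. Run-in patients per ward are 250/8 × 8/32 = 7.8 to 500/8 × 8/32 = 15.6. If ward effects are perfectly stable, the change score is the more precise once the ICC exceeds 1/(n + 1), where n is the number of run-in patients per ward: 1/8.8 = 0.11 to 1/16.6 = 0.06. The article gives no ICC, so the net effect on precision is unknown.

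**Step 5: timetable.** Run-in plus follow-up is 8 + 24 = 32 weeks. Recruitment from 25 April to 2 December 2022 is 221 days, or 31.6 weeks. Weeks 9 to 36 span 28 weeks, 4 more than the 24-week period. Separately, the Abstract and The trial place data collection after the run-in, while Data collection gathers outcomes during it.

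**The case against.** **PDRM may not have started in run-in.** Delivery in run-in rests on one sentence of the abstract, supported by the run-in's stated purpose. The trial and Data collection both attach the word intervention to the later 24 weeks only, and the schedule figure is not shown. If PDRM started after run-in, f = 0 and nothing is lost. This stands as a reason to reconcile the text. It does not remove the concern, because neither section says PDRM is withheld during run-in and the abstract's statement is the more explicit one.

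**The right comparison may already be planned.** Data collection describes an outcome analysis of later admissions, and Statistical analysis does not say that the intervals come only from the change contrast. That is fair. But change from run-in is the only between-arm contrast the section spells out, and nothing gives the follow-up comparison priority.

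**It is a feasibility trial.** The five progression criteria in Table 2 cover ward recruitment, consent, delivery, time to review and data availability. None uses an effect estimate, and the article disclaims power for superiority. This stands and limits the severity.

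**Stronger readings that the article does not support.** A reader might infer that the analysis cancels the intervention effect outright. That needs f = 1, and a settling-in phase suggests something less. A reader might take it as stated that wards are randomised before run-in. Randomisation is placed after ward recruitment and training only; arm-specific delivery in run-in would require prior allocation, but that is an inference. A reader might also take the factor of 4 as the net loss of precision, which step 4 shows it is not. Finally, having different patients in the two periods is an openly stated repeated cross-section. It becomes a problem only when the within-arm change is read as an effect.

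**Conclusion.** The point holds as a should-fix. Taken as written, the abstract, Data collection and Statistical analysis together produce a between-arm contrast that estimates (1-f)E. It is biased towards no effect by an amount the documents do not fix, between 0% and 100% of E. The result assumes a common time trend and no PDRM effect on usual-care wards, and the rate ratios and risks shown are illustrations on assumed values. It depends on PDRM being delivered during run-in, which the abstract states and the other sections leave ambiguous. The within-arm change is not usable as effect evidence on either reading, because patients, calendar time and experience all differ between periods. The decision on progressing to a definitive trial is unaffected.

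**What to change.** 1. State when wards are randomised and when PDRM delivery begins relative to the run-in. Reconcile the abstract with The trial and Data collection on this, and on whether run-in outcomes are collected.
2. Make the between-arm comparison of post-run-in admissions, allowing for clustering and without subtracting run-in values, both the estimate of potential effect and the analysis piloted for the definitive trial. It targets E whatever f is.
3. If PDRM is delivered in run-in, report those data by arm as early-delivery data, not as baseline.
4. Do not use within-arm changes as evidence of effect.
5. Reconcile weeks 9 to 36 with the 32-week duration.
6. Optionally, describe ward balance from aggregate routine data for a window before randomisation. Retrospective routine data were used in the 2018 service evaluation. Such data would cover all patients rather than consenting participants, so they describe a different population, and any outcome that needs notes review would take more than an electronic export.

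Items 1 to 5 are wording changes and need no extra patients. The cost of item 2 is that any precision gained by removing stable between-ward differences is given up.
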